## Abstract

**Background:**

The following protocol pertains to a pioneer study, aiming to investigate how weather sensitivity and walking in different environments affects the psychophysiological responses to the stress of individuals with coronary artery disease (CAD) during rehabilitation (WE_SENSE_THE_NATURE). This randomised control trial will provide fresh insight on the influence of the environmental exposure in CAD patients, as it is seldom investigated in association to the disease. Additionally, findings on the link between personality traits and cognitive functions (especially cognitive flexibility), and weather sensitivity may help reveal a fine-grained perspective on the treatment possibilities for individuals with CAD at risk to stress-vulnerability.

**Discussion:**

The outcomes of this study may have direct clinical applications for the use of different types of exercise environments in cardiac rehabilitation programs. Awareness about the potential influence of weather sensitivity on the psychophysiological reactions to stress in individuals with CAD may contribute to a timely planning and implementation of actions leading to improved medical care services and preventive measures, especially considering the expected weather oscillations and extreme weather events due to unfolding of the climate change.

**Trial registration:**

This protocol has been retrospectively registered in ClinicalTrials.gov with identifier code: NCT06139705 on November 20, 2023.

**Supplementary Information:**

The online version contains supplementary material available at 10.1186/s40359-024-01574-3.

## Background

The environment might influence one’s course of a disease and health prospective through direct exposure to physical, chemical, social, and psychosocial risk factors, as well as indirectly, through behavior-related changes response to those factors [1]. Classical risk factors (pertaining to dietary and lifestyle habits) only partially account for variations in the occurrence, incidence, and mortality of cardiovascular disease (CVD). Therefore, other, less-explored factors need to be taken in consideration when referring to the epidemiology of the disease [2].

Most notably, stress (both physiological and psychological) affects the biological processes involved in the progression of coronary artery disease (CAD) [1]. Stress is associated with a wide range of diseases that involve almost every physiological system. Mounting experimental evidence exists on the link between stress and physiological or psychological functions of individuals, as well as the psychophysiological reactions to stressful and challenging environmental exposures [3–6].

In this regard, physical activity largely contributes to the prevention of CAD, improves the prognosis of patients, and decreases depressive symptoms [7, 8]. Indeed, the restorative effects of walking in nature have been documented and accumulating over the past 30 years, gaining lot of attention over the years [9]. Outdoor exercise, appears to be more beneficial than the same activity in urban settings or indoors, based on some experimental indications from psychological, physiological, and biochemical metrices [9–11]. Nevertheless, some studies and recent systematic reviews or meta-analyses [12, 13] suggest differences in the effects of natural versus urban environments. For example, Mygind and colleagues [14] show that seated relaxation and walking in natural environments has enhanced heart rate variability to a greater extent, than the same activities that were performed in control conditions, even though data about cortisol concentration levels remained inconsistent. In addition, some isolated findings suggest that even short-term visits to nature have a more pronounced effect on perceived stress relief, compared to the built environment, with no marked differences in the decrease of salivary cortisol levels [15].

However, natural environments may not always be restorative, despite the fact that people tend to recover more quickly from stress and mental fatigue in natural than in urban settings [16]. In fact, physical environment can heighten or ameliorate stress, while meteorological factors also cause a certain stress on the human body [17]. Changes in meteorological parameters may affect human hemodynamics and other factors adversely, thereby catalysing the event of an acute coronary syndrome [18]. To this extent, little is known about the restorative or exacerbating potential of natural environments for weather-sensitive (WS) individuals. Concerning reactions to weather variations, people can be divided into two main groups: weather-resistant and WS [19, 20]. The term “weather sensitivity” is used to define the impairment of well-being and/or incidence of symptoms or exacerbations of diseases in response to weather changes [21]. According to the results of our earlier study, almost 50% of individuals with CAD described themselves as being WS [22].

WS profile and the effects of walking in nature on the psychophysiological stress response in individuals with CAD (WE_SENSE_THE_NATURE) is a pioneer study, aiming to investigate how weather sensitivity and walking in different environments affects psychophysiological responses to the stress of individuals with CAD during rehabilitation. The proposed randomised control trial will provide insight on the influence of environmental exposure, as it is seldom investigated in association to heart disease.

Specifically, we aim to explore the link between personality traits and cognitive functioning (especially cognitive flexibility) with WS. Compulsive personality traits and distressed personality profile together represent risk factors that affects mental and physical health [1, 23–28]. Reduced cognitive functioning is also known to negatively impact many aspects of individual functioning, including the psychological, social, and occupational spheres [29, 30]. Studies investigating a set of cognitive, clinical, and personality predictors of functional outcomes of patients with CAD are therefore needed, but seldom investigated integratively. Thus our explorative aim is to understand associations between WS and personality characteristics as well as cognitive functioning in patients suffering from CAD. This exploration may reveal significant information which could help to stratify and apply treatment possibilities available for stress-vulnerable CAD patients. A patient-tailored approach which is timely and appropriate would be much welcome in the face of the rapidly unfolding climate change.

## Methods / design

### Aim

The aim of this study is to investigate how WS and walking in different environments affect psychophysiological responses to the stress of individuals with CAD during rehabilitation.

To achieve the main goal, we will aim to deliver a set of specific objectives:

Determining how walking outdoors (in a natural setting) affects the psychophysiological reactions to stress in individuals with CAD.Determining how walking indoors (in the gym) affects the psychophysiological reactions to stress in individuals with CAD.Investigating the associations between the psychophysiological reactions to stress of individuals with CAD and the walking environment, by accounting for their weather-sensitivity.Understanding the connections between mental flexibility and weather sensitivity in the context of personality characteristics and mental distress.

We hypothesize that: (1) the psychophysiological reactions to stress in people with CAD will differ between the experimental (walking outdoors) and the control group (walking indoors); (2) for the experimental group, we hypothesize that psychophysiological reactions to stress will differ between WS individuals and non-WS individuals, showing more favorable results in the latter subgroup (non-WS individuals); (3) for the control group, we hypothesize that psychophysiological reactions to stress will differ between WS individuals and non-WS individuals, showing more favorable results in the former subgroup (WS individuals). The fourth goal is exploratory and therefore has no hypothesis.

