### Experiment procedure

On the day of the experiment (Fig. 2), we will evaluate the effect of walking in different environments on hemodynamic parameters, stress level (according to cortisol concentration in saliva), and mood. In the morning, the patient will be fitted with a long-term blood pressure device, which will be removed the next morning. In this way, the patient will also receive detailed information about their hemodynamics. Both a collection of saliva samples and a mood assessment will be performed immediately before and after the intervention (walking). A cold pressure test (short immersion of patient’s hand into a cold container) will then be administered, followed by a third mood assessment. The third saliva sample will be collected 20 min after the cold pressure test. Cortisol levels rise progressively after a few minutes (about 10 min) of stimulation and peak between 10 and 30 min after stress termination [32, 33].

Participants in the OUT group will be instructed to keep a comfortable walking speed and to enjoy the walk and the surroundings. Participants in the IN group will be introduced to the treadmill and encouraged to choose a walking speed like that of leisurely outdoor walking. All participants will be informed that they will be accompanied by the researcher (at a distance) during the intervention to monitor their walking time, minimize the impact of social interaction, and control any potential well-being or health problems.

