### Sample size

Based on previous research in this area [45], considering the cortisol response to psychophysiological stress as a primary approach to detect a likely medium difference between groups effect (Cohen d = 0.5) and achieve sufficient power1 (1-ß err prob = 0.95) requires a sample of at least *n* = 82 subjects. Considering possible side variable of weather sensitivity and differences in natural conditions, likelihood of 4% attrition, the sample is planned to be doubled to *N* = 164 subjects. The enrollment duration - one year.

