### Statistical analysis

All statistical analyses will be conducted using the IBM SPSS Version29.0.0.0 (Chicago, IL, USA). Variable distribution of similarity to normal will be assessed visually and using the Kolmogorov-Smirnov and Shapiro‐Wilk tests. Student’s t‐test, Mann‐Whitney test, and/or Wilcoxon rank test will be used for data comparison between groups. General Linear Modelling will be used for multiple dependent variables comparisons. Frequency, dependence, and homogeneity of statistical significance will be tested using the Chi square test, or/and Fisher’s exact test. The probability of equality will be tested using z‐test. Binary, multivariate logistic, linear, and nonlinear regression will be used to test correlations of the study findings adjusting for possible confounders.

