clinical practice - using different types of environments in cardiac rehabilitation. If the hypotheses are confirmed, for weather-sensitive patients with CAD, it might be better to engage in physical activity in an indoor environment than in an outdoor one;sciences and education. Whilst the study will be carried out in Lithuania, it is hoped that the methods used and the results obtained will contribute to a better understanding of the problem analyses and will be useful for future insights and research not only in Lithuania, but also on an international level. It might also provide a foundation for new research studies looking into and beyond traditional risk factors identifying high-risk subgroups of patients with CAD vulnerable to stress.health services’ management - to the government and policymakers in planning and implementing actions to improve medical care services in rehabilitation and post-rehabilitation settings.

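### Cortisol is the outcome that sizes the trial, but the three confirmatory hypotheses are stated on haemodynamics, cortisol and mood together, so the text does not say which result decides them

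*Protocol article*

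**What the plan says.** All references are to the protocol article.

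- **Aim.** Hypothesis 1 (H1) is that "the psychophysiological reactions to stress in people with CAD will differ between the experimental (walking outdoors) and the control group (walking indoors"). Hypothesis 2 (H2) compares weather-sensitive (WS) with non-WS patients in the outdoor arm, "showing more favorable results in the latter subgroup (non-WS individuals"). Hypothesis 3 (H3) makes the same comparison in the indoor arm with the opposite prediction, "showing more favorable results in the former subgroup (WS individuals"). None names an outcome or a time point. Only the fourth goal is called exploratory, so H1-H3 stand equally as hypotheses to be confirmed.
- **Experiment procedure.** On the experiment day the effect of the walking environment is evaluated "on hemodynamic parameters, stress level (according to cortisol concentration in saliva), and mood". There are three saliva samples: before the walk, after it, and 20 min after the cold test.
- **Sample size.** The calculation proceeds by "considering the cortisol response to psychophysiological stress as a primary approach" for detecting a difference between groups.
- **Statistical analysis.** Between-group t and rank tests are listed, and "General Linear Modelling will be used for multiple dependent variables comparisons". Cortisol is not singled out.
- **Discussion.** "If the hypotheses are confirmed, for weather-sensitive patients with CAD, it might be better to engage in physical activity in an indoor environment" than outdoors.
- **Limitation.** The authors regard the trial as a pilot and ask for replication before recommendations are made.

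**The concern.** Which outcome decides a hypothesis belongs in the protocol, and here the sections do not fit together. One section treats cortisol as primary, while the hypotheses treat three domains as interchangeable.

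A split result is foreseeable from the article's own Background. That section reports work in which natural settings raised heart rate variability while cortisol findings were inconsistent. It also reports work in which perceived stress fell more in nature without a marked cortisol difference. If mood differs between arms and cortisol does not, the article does not say whether H1 is confirmed or refuted. Someone following the text could declare confirmation on whichever domain differed, and could do the same for each weather-sensitivity hypothesis. The Discussion then attaches a tentative practice statement for WS patients to confirmation of the hypotheses.

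**Working it through.** **Figure to reproduce.** The article states no error rate for the set of hypotheses, so there is none to reproduce. (The stated n = 82 for d = 0.5 and power 0.95 does not reproduce as a two-arm comparison either: the exact t-test needs 105 per arm two-sided. That is a separate matter and does not affect what follows.)

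**Inputs from the article.** Three hypotheses (Aim); three outcome domains and three saliva samples (Experiment procedure); about 50% WS (Background). With 164 patients and alternating allocation there are 82 per arm, hence about 41 WS and 41 non-WS per arm.

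**Assumptions, not in the article.** 5% two-sided per test; one variable per domain; equal correlation ρ between the domain test statistics, varied from 0 to 0.8; H1, H2 and H3 mutually independent. The last is reasonable: H2 and H3 use different arms, and with balanced WS proportions the simulated correlations among the three contrasts were about 0.01 or less in size.

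**Step 1: H1 alone, any of three domains.**
At ρ = 0: 1 − 0.95³ = 14.3%. For ρ > 0, by simulation of correlated normal statistics with |z| > 1.96: 12.5% at ρ = 0.5 and 9.8% at ρ = 0.8.

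**Step 2: at least one of H1-H3, any of three domains.**
Let a be the Step 1 rate and b the rate when only the predicted direction counts (z > 1.96).
- Either direction: 1 − (1 − a)³.
- H2 and H3 counted only in the stated direction: 1 − (1 − a)(1 − b)².

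| ρ | a | b | Either direction | H2, H3 as predicted |
|---|---|---|---|---|
| 0 | 14.3% | 7.3% | 37% | 26% |
| 0.5 | 12.5% | 6.3% | 33% | 23% |
| 0.8 | 9.8% | 4.9% | 27% | 18% |

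Across both scoring rules and all correlations the range is about 18-37%.

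**Step 3: cortisol alone decides all three, each at 5%.**
Either direction: 1 − 0.95³ = 14.3%. H2 and H3 as predicted: 1 − 0.95 × 0.975² = 9.7%.

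**Step 4: cortisol alone decides H1.**
One fixed contrast: 5%. With a free choice among the three pairwise changes between the three samples: about 12% (within-person correlation 0.3 to 0.7).

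**Step 5: would it be sound to test H2 and H3 only after a significant H1?**
Score outcomes so that higher is better, and let WS and non-WS differ by δ within each arm in the predicted directions. Suppose the crossover is symmetric and WS prevalence is 50%:
- outdoor mean = ½(−δ/2) + ½(+δ/2) = 0
- indoor mean = ½(+δ/2) + ½(−δ/2) = 0

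H1 is then null although H2 and H3 are both true. Simulated with 41 per subgroup and δ = 0.5 SD, the H1 test is significant about 4% of the time, while H2 and H3 each have about 61% power. At δ = 0.6 SD the gate still opens about 4% of the time, with power about 77% for each.

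**The case against.** **The missing multiplicity procedure could sit elsewhere.** Test order, alpha allocation and the exact change score are often left to an analysis plan or full protocol, and neither is shown. This stands: the absence of an adjustment is not the finding. What remains is that the published hypotheses and the published sizing rest on different outcome sets.

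**Cortisol is named.** A reader might infer that the article has no deciding outcome at all. It does not support that. The Sample size section names the cortisol response for a between-group difference, most naturally outdoor v indoor. The time point is not wholly open either, since the third sample is justified by the timing of the cortisol peak after stress. So the 12% in Step 4 is an outer case, and one natural reading of H1 is already at 5%.

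**The size depends on assumptions.** A reader might take 23-33% as the trial's error rate. Those two figures are two scoring rules at one assumed correlation. If the General Linear Model were a multivariate omnibus test per hypothesis, the rate for the three would be about 14%. More than one variable per domain would raise it. A footnote to the power statement is not shown, so nothing should rest on alpha being unstated.

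**The practice statement is guarded.** It is conditional on the hypotheses in the plural and worded as a possibility, and the Limitation section calls the trial a pilot. If both H2 and H3 must hold, two false confirmations at ρ = 0.5 have probability about 0.063² = 0.4% in the stated directions, or 0.125² = 1.6% in either. The rate for at least one false confirmation therefore does not measure the risk to that statement. This softens the consequence. It does not settle what confirms H1.

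**Conclusion.** The concern holds in a limited form. The trial is sized on cortisol, but H1-H3, all confirmatory, are stated on three outcome domains, and neither the Aim nor the Statistical analysis section carries cortisol forward or fixes the cortisol change that decides. Under 5% per test, one variable per domain and correlation 0.8 to 0, taking the text literally gives about 10-14% false confirmation for H1 and about 18-37% for at least one of H1-H3. The inflation is not universal: it is about 10-14% if cortisol alone decides all three, and absent for H1 on one fixed cortisol contrast. The point deserves correction before analysis. With the pilot label and the guarded practice wording, it is not a threat to the trial as a whole.

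**What to change.** - In the Aim and Statistical analysis sections, state that H1 (outdoor v indoor) is decided by one fixed cortisol contrast at two-sided 5%, for example the sample 20 min after the cold test analysed against the pre-walk sample.
- Label haemodynamic and mood outcomes secondary, reported with estimates and confidence intervals and not used to declare a hypothesis confirmed.
- Test H2 and H3 on the same cortisol variable with a Holm adjustment that does not depend on H1, or label them exploratory as goal 4 already is. Do not gate them on H1: Step 5 shows that their opposite predictions can cancel the main effect and block a true weather-sensitivity result.
- Word the practice statement in the Discussion as hypothesis-generating, in line with the Limitation section.

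This is a change of wording before analysis and needs no new patients, visits or data. The price is that a mood or blood pressure difference alone can no longer be presented as confirming H1. If Holm is used, H2 and H3 also lose a little power.

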11.	Cold pressure stress	Cold pressure test (CPT) [43]	CPT will be used to induce acute stress. Temperature and other environmental stressors are known to affect BP and heart rate. In this activity, participants will be performed the cold pressure test to demonstrate the changes in BP that follow an environmental stress. For cold stress, the subject will immerse his or her right hand in the ice-water bath (4 °C) to a point just above the elbow for 2 min. BP measurements will be obtained using a long-term BP device – the SOMNOtouch NIBP monitor on the wrist of the left hand at 0, 1, 2, and 4 min after the right hand will be removed from the ice-water bath.	Up to 8 min
12.	Pain intensity	Visual Analog Scales (VAS) [42]	After the CPT, study participants will be debriefed about the purpose of the study and the subjective measure of perceived efforts and perceived difficulty of the CPT will be collected by using VAS. The scales ranged from 0 (maximum difficulty/efforts) to 100 (minimum difficulty/efforts). VAS were chosen based on its applicability in experimental clinical studies and common use in combination with CPT [44].	Up to 1 min

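### Hypotheses 2 and 3 compare weather-sensitive with non-sensitive patients inside one arm, so a general trait difference can confirm H2 or work against a true H3 whatever the walking environment

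*Protocol article*

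**What the plan says.** All references are to the protocol article.

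- **Aim.** H1 compares outdoor (OUT) with indoor (IN) walkers and does not involve WS. H2 reads "for the experimental group, we hypothesize that psychophysiological reactions to stress will differ between WS individuals and non-WS individuals" and predicts better results in the non-sensitive. H3 is the matching comparison among indoor walkers and predicts better results in the sensitive.
- **Randomisation.** Only the walking environment is assigned. WS is a baseline questionnaire result (Measurements, Table 1, step 1).
- **Background.** WS is defined as impaired well-being and/or "incidence of symptoms or exacerbations of diseases in response to weather changes". Almost half of the CAD patients in the group's earlier study called themselves sensitive.
- **Measurements, Table 1, step 11.** The stressor is a hand in water at 4 °C, introduced with "Temperature and other environmental stressors are known to affect BP and heart rate". Under Experiment procedure, the third mood rating and third saliva sample follow it.
- **Sample size.** The calculation is "to detect a likely medium difference between groups effect (Cohen d = 0.5") with "1-ß err prob = 0.95"; then "the sample is planned to be doubled to *N* = 164 subjects".
- **Discussion, first of the three fields of contribution.** If the hypotheses hold, indoor activity might be better than outdoor activity for weather-sensitive patients.

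**The concern.** H2 and H3 are meant to show how the walking environment acts on sensitive and non-sensitive patients. Neither compares environments. Each compares two self-selected kinds of patient who walked in the same place. If sensitive patients react more strongly to stress in general, they will look worse outdoors and worse indoors. The outdoor result then matches H2, although where they walked played no part. The indoor result counts against H3, even if indoor walking does help them.

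The choice of stressor makes a general difference plausible: patients grouped by their response to weather are tested with cold water. Adjustment for confounders cannot remove the difference, because the trait is the grouping variable itself.

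What is at stake is the Discussion's statement on indoor v outdoor exercise for sensitive patients. That is an OUT v IN comparison within sensitive patients, and none of the three hypotheses tests it.

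**Working it through.** **The plan's own figure.** For d = 0.5 and power 0.95 at an assumed alpha of 0.05, two equal groups need 104 to 105 each two-sided (208 to 210 in total), or 87 to 88 each one-sided. The stated 82 is not reproduced. That is a separate matter; only the planned total of 164 is used below.

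**Inputs.**
- 164 patients (Sample size), allocated 1:1 (Randomisation): 82 per arm.
- About 50% sensitive (Background): 82 × 0.5 = 41 WS and 41 non-WS per arm.
- Two-sided alpha 0.05: assumption, as the article gives none.
- Trait difference b, with WS worse by b SD in both arms: assumption, 0.2 to 0.8 SD. The article gives no value.

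**H2 with no environment effect.** The standard error of a within-arm contrast is √(2/41) = 0.221 SD. The noncentrality is b/0.221, the critical t on 80 df is 1.990, and the probabilities come from the noncentral t distribution.

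| b (SD) | noncentrality | H2 confirmed as stated | H3 confirmed as stated |
|---|---|---|---|
| 0 | 0 | 2.5% | 2.5% |
| 0.2 | 0.91 | 14% | 0.2% |
| 0.3 | 1.36 | 27% | 0.05% |
| 0.4 | 1.81 | 43% | 0.01% |
| 0.5 | 2.26 | 61% | about 0 |
| 0.8 | 3.62 | 95% | about 0 |

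The stated 4% attrition leaves 164 × 0.96 = 157, or about 39 per cell. The figure at 0.3 SD is then 26%, so little changes.

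**Both hypotheses together.** The arms are independent, so the probabilities multiply. At b = 0.3 the product is 0.268 × 0.00048 = 0.013%, below the 0.025 × 0.025 = 0.06% expected with no trait difference.

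**A true H3 effect of 0.5 SD, opposed by b.** The net difference is 0.5 − b.
- b = 0: power 61%.
- b = 0.2: net 0.3 SD, power 27%.
- b = 0.3: net 0.2 SD, power 14% in the stated direction (15% counting either direction).
- b = 0.5: net 0, so 2.5%.

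With the mirror-image 0.5 SD effect outdoors, power for H2 rises to 88%, 95% and 99% at b = 0.2, 0.3 and 0.5.

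**Interaction.** Write the WS minus non-WS contrast as b + e(OUT) outdoors and b + e(IN) indoors. The difference is e(OUT) − e(IN), and b cancels. Its standard error is √(4/41) = 0.312 SD, and the critical t on 160 df is 1.975.
- Pure trait difference of 0.3, 0.5 or 0.8 SD: rejection in 4.9%, 4.9% and 5.0% of 40,000 simulated trials.
- Predicted crossover of 0.5 SD each way: contrast 1.0, noncentrality 1.0/0.312 = 3.20, power 89% whatever b is.
- Crossover of 0.25 SD each way: contrast 0.5, noncentrality 1.60, power 36%.

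**Why H2 plus H3 does not give the Discussion's conclusion.** Take mean responses in SD, higher being worse:

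| | OUT | IN | OUT − IN |
|---|---|---|---|
| WS | 0 | 0 | 0 |
| non-WS | −0.5 | +0.5 | −1.0 |
| WS − non-WS | +0.5 | −0.5 | |

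H2 and H3 are both true, yet sensitive patients do equally well in either place. All of the crossover comes from the non-sensitive.

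**The case against.** The strongest reply is that the two hypotheses guard each other. They predict opposite directions, so a trait difference common to both arms cannot produce the pattern, and the Discussion makes its recommendation conditional on the hypotheses in the plural. The first part stands, as the 0.013% shows. It does not rescue the conclusion, because joint confirmation is compatible with no OUT v IN difference at all in sensitive patients. H2 is also a hypothesis in its own right and can be reported alone.

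Several stronger readings are tempting, and the article does not support them:

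- *A trait difference alone masks H3.* With no environment effect, H3 is simply false and there is nothing to mask. Masking needs a true environment-specific effect.
- *Sensitive patients must react more to ice water.* WS is defined by weather changes, not by the environment at large, and nothing in the article shows stronger cold reactivity. It is plausible and no more.
- *H2 and H3 concern only the cold test.* The Aim speaks of reactions to stress generally, and saliva and mood are also taken just before and after the walk.
- *The design is confounded.* It is not. The four cells can separate trait from environment; the fault is in the wording of the hypotheses.
- *The missing interaction term is an error.* Objective 3 asks about the environment while accounting for WS, general linear modelling is named, and an analysis plan that is not shown may hold the term.

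It is also fair that the aim includes WS itself, so a WS difference is of interest, and that the Limitation section calls this a pilot. Both argue for reporting the within-arm contrasts, but not for reading them as environment effects.

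**Conclusion.** The concern holds as a fault in how H2 and H3 are framed. As worded, H2 can be met, and a true H3 opposed, by a difference between kinds of patient that has nothing to do with where they walked. At an assumed 0.3 SD trait difference, H2 is confirmed in about 27% of trials with no environment effect, and power for a true 0.5 SD H3 effect falls from 61% to about 15%. These figures rest on 41 patients per cell, a two-sided 5% level and an assumed trait size. They show what follows if such a difference exists, not that it does.

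Separately, and whatever the trait size, the Discussion's statement about sensitive patients does not follow from H2 and H3 even when both are confirmed.

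**What to change.** 1. Restate H2 and H3 as one formal test of the WS-by-environment interaction: the WS minus non-WS contrast in OUT minus the same contrast in IN, with its confidence interval. A merely larger number in one arm should not count as support.
2. Base the Discussion's statement on OUT v IN within sensitive patients, also with a confidence interval. The interaction alone cannot show which patients drive a crossover.
3. Report the two within-arm WS contrasts descriptively, and state beforehand that a similar difference in both arms is a trait effect.

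Making the readings taken before the cold test the main readout would not solve the problem. They can differ by trait in both arms too, and they come before the stressor whose response is in question.

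**Cost.** Wording and analysis only; no new data or patients. The interaction has 89% power for the predicted crossover at 0.5 SD each way (a contrast of 1.0 SD) but about 36% at 0.25 SD each way (0.5 SD). The OUT v IN comparison within sensitive patients has 41 v 41 and so 61% power at 0.5 SD. The trait difference cancels only if it is the same in both arms on the scale analysed, so that scale should be fixed in advance.
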